## **5.3 Vaccinated persons**

The individual is defined as vaccinated if he/she has received at least one dose of A(H1N1)v vaccine, irrespective how much time has elapsed since the vaccination.

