## **2 Objectives**

### **2.1 Primary objective**

- To determine the effectiveness of an A(H1N1)v influenza vaccination in preventing the first episode of laboratory-confirmed infection with the novel, pandemic influenza A(H1N1)v virus among community-dwelling and recently vaccinated adults as compared to unvaccinated adults from a cohort of at least 4,000 persons

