## **5.2 Laboratory confirmation of influenza A(H1N1)v virus infections**

Cases of laboratory confirmed A(H1N1)v influenza are defined as events, where an individual belonging to the effectiveness and safety cohort and presenting with ILI defined in chapter 5.1. has A(H1N1)v influenza virus identified from a combined nasal and throat swab specimen obtained within five days after onset of the symptoms by methods described in chapter 10.2.1

- at least a 4-fold increase in A(H1N1)v influenza-specific antibody titers in serum specimens between the acute phase (0 to 5 days after onset of the symptoms) and convalescent phase (2-3 weeks after the acute phase serum sample) serum specimens will be used as additional information, if the person is unvaccinated or if at least 4 weeks have elapsed since receiving the last dose of A(H1N1)v vaccine at time of the acute phase sampling, but this is not a criteria for defining cases of laboratory confirmed influenza.

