### **11.2 Sample size considerations**

Based on recent questionnaire data from Finland, as part of FLUMODCONT (pandemic FLU MODelling CONTainment strategies),project, the assumption is that, if offered the vaccine, 90% will take it. Hence the expected number of unvaccinated persons in the study cohort is 400. Furthermore, it is assumed that during the first wave of the A(H1N1)v pandemic, which is the planned period of follow-up in this study, 20% of the unvaccinated become infected by the A(H1N1)v virus, i.e. 80 expected cases. The assumed effectiveness of the vaccine is 70%. The study is

powered to demonstrate the effectiveness of the vaccine such that the lower level of the 95% confidence interval is above 50%, which is regarded as the level of clinical relevance for the A(H1N1)v vaccine. With a random sample size of 4,000 the power of the study is 95%. High power for the effectiveness evaluation is preferred, since taking into account potential confounders, as well as possible unbalance in the age distribution of the study cohort (see Section 3) will lower the power.

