### **11.3 Statistical methods for analyses**

The incidence of the laboratory-confirmed H1N1 pandemic influenza will be calculated as the number of cases divided by the person-time at risk, where person-time at risk is defined as compliance to the regular contacts. Periodic variation of incidence in calendar time will also be explored both in vaccinated and unvaccinated groups. Event-history analysis methods will be used for the evaluation of the effectiveness of the vaccine, where the risk of acquiring A(H1N1)v-influenza will be compared between the vaccinated/unvaccinated states, by accounting for calendar time and other potential confounders. Vaccine effectiveness will be calculated as 1- relative risk. For the vaccine adverse events, case-series method will be used for comparing the incidences between risk and non-risk periods. Descriptive analysis will be conducted for the immunogenicity cohort, such as calculation of geometric mean titres and percentages over pre-defined thresholds. Due to the nature of the study (see Section 3), other descriptive analyses and tests of hypotheses may also be carried out but the choice of subsequent hypotheses will be data dependent

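### With no lag between the dose and vaccinated status, the primary effectiveness estimate is diluted by infections that occur before protection can develop, by an amount that runs from negligible to decisive

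*Protocol*

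**What the plan says.** - **Exposure (Protocol 5.3).** A person is vaccinated if he or she has "received at least one dose of A(H1N1)v vaccine, irrespective how much time has elapsed since the vaccination". This is a positive rule and not a detail left open.
- **Objective (Protocol 2.1).** The comparison is of "community-dwelling and recently vaccinated adults as compared to unvaccinated adults". The word for recency has no time limit attached, and 5.3 supplies none.
- **Analysis (Protocol 11.3).** In an event-history analysis the risk of influenza "will be compared between the vaccinated/unvaccinated states, by accounting for calendar time and other potential confounders". The effect measure follows: "Vaccine effectiveness will be calculated as 1- relative risk". The section mentions no lag, no separate early post-dose state and no sensitivity analysis on time since dose.
- **Sample size (Protocol 11.2).** The inputs are 4,000 persons, 90% uptake (400 unvaccinated), 20% infected among the unvaccinated (80 cases) and effectiveness of 70%. Success is a lower 95% limit above 50%, described as the level of clinical relevance, and the stated power is 95%. Nothing is allowed for cases soon after the dose.
- **Timing (Protocol 3, 6 and 15).** Vaccination takes place during the study period. Enrolment may start once the epidemic has begun or once vaccination has been decided. Section 3 stresses that the timing of the peak is uncertain.

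**The concern.** Read together, 5.3 and 11.3 switch a person from unvaccinated to vaccinated on the day of the dose. Handling vaccination as a state that changes over time avoids immortal-time bias. It does not prevent dilution, because days with no or partial protection are pooled with protected days.

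Section 11.2 sets its 50% threshold as a relevance level for the vaccine and assumes 70% with no discount. The quantity it has in mind is therefore protection from an effective vaccination. Measured against that, the planned estimate is too low by an amount that varies with how far the campaign and the wave coincide. An effective vaccine could miss the plan's own criterion for that reason alone.

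**Working it through.** **Step 1: reproduce the stated power.** The inputs from 11.2 are 80 cases in 400 unvaccinated and 3,600 × 0.20 × 0.30 = 216 cases in 3,600 vaccinated. Success means that the upper 95% limit of the relative risk (RR) is below 0.50. A Wald test on p1 − 0.5·p0 gives 96.1%. Simulated counts with exact conditional limits give 94.8% (Poisson) and 96.3% (binomial). The stated 95% is reproduced. The simpler formula used in step 3 runs slightly high at RR = 0.30 (97.4% and 98.9%), so the power figures below are if anything generous.

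**Step 2: dilution.** Let f be the share of infection pressure on vaccinated time that falls in a window with no protection, with 70% protection afterwards. Then

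RR = f × 1 + (1 − f) × 0.30, so VE = 1 − RR = 0.70(1 − f).

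**Step 3: power at the diluted RR.** Power = Φ(ln(0.50/RR)/SE − 1.96), with two versions of SE:

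- binomial: SE² = 1/80 − 1/400 + 1/(720·RR) − 1/3,600
- event-based: SE² = 1/80 + 1/(720·RR)

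Example with f = 10%: RR = 0.10 + 0.90 × 0.30 = 0.37 and ln(0.50/0.37) = 0.301. The SEs are 0.116 and 0.127, giving power of 74% and 66%.

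| f | VE | Power |
|---|---|---|
| 0 | 70% | 97–99% |
| 5% | 66.5% | 87–93% |
| 7.7% (14 of 182 days at constant incidence) | 64.6% | 77–84% |
| 10% | 63% | 66–74% |
| 20% | 56% | 17–20% |
| 28.6% | 50% | 2.5% |
| 30% | 49% | about 2% |

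**Step 4: what f could be.** This needs assumptions, since the protocol gives no lag, campaign length or wave timing. Assume 3,600 persons vaccinated evenly over 8 weeks, 400 never vaccinated, a bell-shaped wave with SD 3 weeks, and a 20% attack rate without vaccination. Assume no protection inside the window and 70% after it. Time before the dose counts as unvaccinated, as in 11.3. The rate ratio is Mantel–Haenszel, stratified by calendar day. Peak weeks count from the start of the campaign.

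| Wave peak | VE (power), 14-day window | VE (power), 7-day window |
|---|---|---|
| Week 8 | 49% (2%) | 60% (about 50%) |
| Week 12 | 65% (82%) | 68% (94%) |
| Week 14 | 69% (95%) | 69–70% (97%) |
| Week 16 | 70% (97%) | 70% (97–98%) |

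**Step 5: separate the window.** Taking it out of the contrast returns VE = 70% in every row, with power of about 97–98%.

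**Step 6: cases removed.** With a 14-day window and a peak at week 8, about 113 of 272 vaccinated cases (113/272 = 42%) fall inside the window. At week 12 the figure is about 30 of 249 (12%), and at week 16 about 2 of 234 (1%).

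**The case against.** The strongest reply is that the any-time definition is deliberate. This is an observational evaluation of a national campaign, and the effect of having received a dose, early infections included, is a legitimate programme-level quantity. Dilution moves the estimate toward no effect, so it cannot manufacture effectiveness. A statistical analysis plan may also add a lag. Of this, the first part stands: the estimate is a valid answer to that different question. But 11.2 judges it against a relevance level for the vaccine and assumes an undiluted 70%, so the two do not match. A lag added later would depart from the rule that 5.3 states.

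Three further objections stand and limit the point:

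- **Overlap is possible but not stated.** Section 6 places vaccination in the study period, and section 15 allows enrolment to begin with either the epidemic or the decision to vaccinate. If the wave follows the campaign by several weeks, the dilution is negligible.
- **The direction is not certain in full.** People who are ill may put off vaccination, which lowers incidence just after the dose and partly offsets the dilution. That is another reason to look at the window separately.
- **The serology rule is not evidence about protection.** A reader might infer that the protocol contradicts itself, because 5.2 uses a titre rise in vaccinated persons only "if at least 4 weeks have elapsed since receiving the last dose of A(H1N1)v vaccine". That condition is best read as keeping vaccine-induced titres apart from infection. The 4-week sample in 8.2 times an immune measurement. Neither says when protection starts, and neither supports any particular lag.

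**Conclusion.** The point holds. Followed as written, 5.3 and 11.3 dilute the primary estimate, as a measure of the vaccine's protection, to about 0.70(1 − f), and nothing else in the protocol corrects this. In the scenarios above the estimate ranges from 70% down to 49%, and power from nearly the stated 95% down to about 2%. These figures assume no protection for 7 or 14 days, an 8-week campaign and a wave with SD 3 weeks, and they ignore deferral of vaccination by people who are ill.

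A reader might infer that the study is bound to miss its criterion, or that its result would reflect timing and not the vaccine. The protocol supports neither. It does not say that campaign and wave will coincide, and the estimate depends on the vaccine's effect as well as on f. The defect is that the primary result is left exposed to an overlap the sponsor cannot foresee, when vaccination data already being collected would remove that exposure.

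**What to change.** In 11.3, with a cross-reference from 5.3, define three time-varying states for the primary effectiveness analysis:

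1. unvaccinated, up to the first dose;
2. an early post-dose window of a length fixed in advance, kept as its own category outside the primary contrast (for example 14 days, with 7 days as a sensitivity analysis);
3. vaccinated, after that window.

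Keep the any-time definition as a sensitivity analysis. Report the early-window estimate as a bias check: little effect is expected there, and a clear departure would point to deferral of vaccination or other confounding. Fix the window length before the timing of cases is known, because 11.3 already allows later hypotheses to depend on the data.

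The cost is a change of wording and one recoded covariate. Sections 6 and 8.1 already provide for vaccinations to be recorded individually and drawn from the health centre system. The downside is that early post-dose cases leave the primary contrast. They are few if the wave follows the campaign, but about 40% of vaccinated cases under strong overlap (113 of 272 with a week-8 peak). Power for the 50% criterion still rises in that case, from about 2% to about 97%, because the cases removed are those that carry the dilution.

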## **6 Vaccinations**

It is anticipated that an A(H1N1)v vaccination campaign is conducted in the study area during the study period. The study subjects represent the target population of such a vaccination campaign and will thereby be offered at least one dose of A(H1N1)v vaccine during the study period by Tampere health centre. An agreement will be made with the health centre on recording the vaccinations individually in the electronic medical records of the health centre or into another database even during mass vaccinations.

## **7 Enrolment**

### **7.1 The cohort for assessing the effectiveness and safety of the vaccine (total study cohort)**

Individuals in the eligible population will be invited to participate in the study, e.g. by sending invitation letters home and by announcing in media, workplaces and/or relevant health care settings until 4,000 subjects fulfilling the eligibility criteria have been enrolled to the effectiveness cohort.

All individuals who volunteer to participate in the study will be invited to a baseline study visit. During this visit the study design and procedures are explained to the subjects, the eligibility will be assessed and a written informed consent will be obtained, including permission to collect of nasal and throat swabs and paired blood samples in case of acute ILI and permission to collect health information on baseline and outcome medical conditions and vaccinations from existing medical registers and medical records. In addition, subjects are requested to comply with weekly contacts by the study staff by SMS, email or phone call.

At the enrolment visit, baseline data and self-reported medical history, including demographics, occupation, co-morbidities, medication, vaccinations and pregnancy are collected.

### **7.2 The subcohort for assessing the immunogenicity and safety of the vaccine (immunogenicity cohort)**

A subgroup of 200 individuals will be recruited to participate in the cohort for assessing the immunogenicity and safety of the vaccine. Participation is offered to those persons who participate the main study (total study cohort) and intend to take the A(H1N1)v vaccine during the vaccination campaign according to the national recommendations for the population. The design and procedures for following the immunogenicity and safety of the vaccines will be explained to the subject and the eligibility will be assessed at the baseline visit. For persons who volunteer to participate in the immunogenicity study, a study visit will be arranged immediately before the first vaccination. During this visit the baseline information will be updated, the eligibility to the immunogenicity study will be reassessed, and a specific written informed consent will be obtained, including pre- and

post-vaccination blood samples for measuring immunogenicity of the vaccine. The consent also comprises reporting serious and important adverse events as well as adverse events with special interest (8.3.1) for a period of 6 months after the last vaccination, and permission to verify the diagnoses in medical records.

## **8 Study outcome assessment**

### **8.1 Assessment of effectiveness**

At enrolment, all 4,000 subjects participating in the effectiveness and safety cohort will be instructed to detect signs of ILI, defined in chapter 5.1. If ILI is present, the participants are instructed to contact the study staff immediately to have nasal and throat swab specimens and a blood sample taken as soon as possible, preferably within 3 days and at least within 5 days after the start of symptoms. Subjects are asked to fill in a diary in case of ILI to characterize the start of symptoms and clinical features of the disease. In addition, all study subjects will be contacted weekly by SMS, if possible, or by email or phone call in order to query any current or previous symptoms of ILI.

In case of ILI, an acute phase visit will be arranged 0 to 5 days after the onset of symptoms, either at the home of the subject or in the premises of collaborating health care settings or at a special study clinic established for the study. Nasal and throat swabs will be obtained by a qualified study nurse or physician, to define the cases of laboratory confirmed A(H1N1)v influenza (5.2). In addition, 10 ml of venous blood will be drawn at the acute phase. Clinical features of ILI will be recorded using the diary as an aid and a convalescent visit will be scheduled 2-3 weeks after the acute phase visit. Another diary will be given for follow up of the course of the disease. At the convalescent visit, 10 ml of venous blood will be drawn for measurement of the increase in A(H1N1)v virus specific antibody levels, and further information of the disease will be collected using the diary as an aid. After the first occurrence of laboratory-confirmed A(H1N1)v influenza case, no subsequent individual follow-up will be performed for the effectiveness outcome, i.e. for ILI.

The information regarding A(H1N1)v vaccination will be obtained from the health care data system of Tampere health centre.

### **8.1.1 Assessment of the severity of laboratory-confirmed A(H1N1)v pandemic influenza cases**

Information on potential missed cases will be collected by weekly contacts to study participants and by collecting the positive laboratory test results for A(H1N1)v virus from the data bases of the Tampere city and TAUH and from the Communicable Disease Register of THL.

To evaluate the severity of the disease, medical records of Tampere city and TAUH will be visited for cases defined in chapter 5.2. The clinical features of the disease and medical consultations will be asked at the acute and convalescence phase visits during ILI using the diary as an aid. If needed and possible, medical record will be requested from other than collaborating health care settings as well. Additional information on infections related to A(H1N1)v influenza may be requested from the Communicable Disease Register (e.g. invasive bacterial diseases).

## **8.2 Assessment of immunogenicity**

From the subgroup of the 200 persons participating in the cohort for assessing the immunogenicity of the A(H1N1)v vaccine, 60 ml of venous blood will be drawn at the day of (and before) the first vaccination. At a visit scheduled at 4 weeks after vaccination, 60 ml of venous blood will be drawn for assessment of humoral and cellular immunity. Immunogenicity will be assessed as the fold-increase between pre- and post-vaccination immune responses. If the national vaccination strategy will include two doses of A(H1N1)v vaccine, similar pre-vaccination blood sample (60 ml) will be drawn at the day of the second vaccination and a post-vaccination blood sample (60 ml) will be obtained 4 weeks after the second vaccination, for assessing the humoral and cellular immune reaction to the second vaccine dose. A blood sample (60 ml) for assessing the long term immunity level is scheduled to be obtained 6 months after the administration of the last vaccine dose.

## **8.3 Assessment of safety**

The safety of the A(H1N1)v vaccine will be followed from health care registers in the total study cohort of 4,000 study subjects and in the immunogenicity cohort, by interview

at the study visits. Baseline medical conditions and medications are recorded at the time of enrolment, and permission to verify the diagnosis from medical records is included in the consent. Permission to verify background data from medical records will also be requested.

### **8.3.1 Safety outcome events**

The list of pre-defined safety outcomes will be adapted from the list of adverse events recommended by European Medicines Agency (EMA) to be followed during pandemic vaccination (4,5). They comprise:

Serious (unexpected) adverse reactions

Adverse events of special interest (AESI), e.g.:

- severe allergic reactions,
- convulsions,
- neuritis,
- encephalitis,
- vasculitis,
- Guillain-Barré Syndrome,
- other demyelinating disorders,
- Bell's palsy,
- vaccination failures

The list may be flexibly adapted according to the information arising nationally and internationally, e.g. by spontaneous reporting of adverse events, experience from vaccination and studies or new recommendations of relevant authorities.

### **8.3.2 Outcome events from the health centre and hospital registers**

Data recorded in the electronic health care data systems during the visits of the study participants to Tampere health centre, Tampere city hospital and Tampere University hospital (TAUH) during the study period will be collected. These data comprise e.g. reasons of the visits, diagnoses made at them, referrals to hospitals, polyclinics and specialists, hospitalisations, emergency room visits and possible cases of death, laboratory records etc. Individual medical records will be visited for additional information, if needed.

### **8.3.3 Outcome events spontaneously reported to the register of adverse reactions following immunisation**

Finnish health care professionals are responsible for reporting serious and/or unexpected adverse reactions following immunisation (AEFI) to Unit of Vaccination Programme (ROHY) of the National Institute for Health and Welfare (THL) by using a form (AEFI form) designed for this purpose (decree no. 421/2004 given by the Ministry of Social Affairs and Health). In addition, a specific form with pre-defined events with special interest will be established for reporting adverse events after vaccination with A(H1N1)v vaccines. ROHY enters information on these reports to an electronic register of adverse reactions following immunisation (AEFI register), which will be an additional method for collecting safety data during the study period.

The healthcare professional will send the AEFI report form by mail or by fax to ROHY without undue delay. In urgent cases the reporting can be also done by phone. Additional or follow-up information relating to the initial suspected adverse event report is also to be completed and submitted with an AEFI form immediately.

If ROHY receives a report of AEFI considered to fulfill the criteria of a serious adverse event (SAE, definition 9.1) after A(H1N1)v vaccination of a participant of the total study cohort, the study staff will be notified by phone immediately and the report will be sent by fax to the investigator and/or designate of the study as soon as possible. The non serious adverse events and AESI cases will be reported to the investigators and/or designate on regular basis without expedition.

### **8.3.4 Outcome events reported by the participants of the immunogenicity cohort**

The 200 subjects participating in the immunogenicity cohort are asked to report the occurrence of serious and important adverse events as well as AESI occurring during the study period up to 6 months after the last vaccination. For this reason, a diary will be given at the first study visit. The diagnoses and details of the events will be verified from medical records, if needed and possible.

## 9 Serious adverse events (SAE) reporting

### 9.1 Definition of SAE

An adverse event is any untoward medical occurrence in a patient or clinical investigation subject administered a pharmaceutical product and which does not necessarily have a causal relationship with this treatment. An adverse event (AE) can therefore be any unfavourable and unintended sign (including an abnormal laboratory finding), symptom, or disease temporally associated with the use of a medicinal product, whether or not related to the medicinal product.

An adverse event is defined as 'serious' when it meets one of the following criteria:

1. results in death,
2. is life-threatening,
  - The term 'life-threatening' in the definition of 'serious' refers to an event in which the subject was at risk of death at the time of the event. It does not refer to an event which hypothetically might have caused death, if it were more severe.
3. requires hospitalisation or prolongation of existing hospitalisation,
  - Hospitalisation signifies that the subject has been detained (or involving at least an overnight stay) at the hospital or emergency ward for observation and/or treatment that would not have been appropriate in the physician's office or outpatient setting. If a complication that occur during hospitalisation prolongs hospitalisation or fulfils any other serious criteria, the event is serious. When in doubt as to whether hospitalisation occurred or was necessary, the event should be considered serious. Hospitalisation for elective treatment of a pre-existing condition that did not worsen from baseline is not considered a SAE.
4. results in persistent or significant disability/incapacity
5. is a congenital anomaly/birth defect in the offspring of a study subject.

In addition, medical or scientific judgement will be exercised in deciding whether an adverse event is serious in other situations. Important medical events that may not be immediately life-threatening or result in death or hospitalisation but may jeopardize the subject or may require medical or surgical intervention to prevent one of the other outcomes listed in the above definition, will also be considered serious. Examples of such events are invasive or malignant cancers, intensive treatment in an emergency

room or at home for allergic bronchospasm, blood dyscrasias or convulsions that do not result in hospitalisation.

